### Aim

The aim of this study was to test the hypothesis that a motivational and behavioral intervention is more effective than a leaflet for promoting participation in physical activity at three months follow-up among insufficiently active postnatal women. Secondary aims are:

1. To test efficacy at six months follow-up (three months post-intervention),

2. Identify the potential impact of the intervention on physical and psychological health and well-being,

3. Examine the utility of psychological mediators for predicting change in physical activity participation,

4. Assess acceptability of the intervention.

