### Sample size

Based on calculations carried out by an independent statistician, 31 participants per group are required in order to detect an effect of 63.83 minutes/week of moderate-vigorous physical activity participation. This assumes power of 90%, 5% significance level with a two-sided unpaired *t*-test to detect change from pre- to post-test between the intervention and control group using a pooled standard deviation of 75 minutes/week. This sample size calculation is based on data from a previous study comparing a 12-week physical activity intervention in insufficiently active breast cancer survivors with usual care [35]. Comparable to the present study, the main outcome in that study was change in weekly minutes of moderate-vigorous intensity physical activity from baseline to three months measured using accelerometers [35]. This study was used as no previous reports of postnatal physical activity promotion interventions had used accelerometers to measure change in physical activity behavior. An increase of 60 minutes of moderate-vigorous physical activity (for example, brisk walking) per week is clinically significant for cardiovascular health [36]. Assuming a 20% dropout (in line with similar studies [14,17]) up to 76 postnatal women will be sought.

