#### Data analysis

Actilife 5 will be used to analyze accelerometer data in the following ways: ‘raw’ accelerometry output (that is, counts per minute (cpm) averaged over the measurement period), time (minutes) spent in moderate to vigorous intensity physical activity per week, continuous bouts of at least 10 minutes of moderate-vigorous physical activity (MVPA) and, percentage of time spent in MVPA. The calculation of MVPA is based on accepted cut-points for adult women in free-living conditions [65-67]. However, there is wide variation in the ability of cut-point equations to accurately assess physical activity in different intensity zones. Cpm is, therefore, an important measure as it provides an estimate of change in total physical activity and has been validated in free-living conditions against criterion methods, such as energy expenditure [68].

Trial data will be analyzed according to intention-to-treat principles with all participants included according to initial group allocation. To minimize the number of statistical tests conducted, Analysis of Covariance (ANCOVA) will be used with a repeated measures design and group allocation as a between groups factor. Covariates, which have been shown to influence physical activity participation, will be included (for example, participant’s age, participant’s BMI and physical activity stage of change). Population-specific covariates (for example, infant’s age and number of children, and so on) will also be added to the model. Bonferroni *post-hoc* testing will be used to investigate intervention efficacy (between-groups change to three months) and assess maintenance effects (whether change is sustained to six-month follow-up). Statistical analysis will be conducted on all secondary outcomes, also using this approach.To assess whether change in the main outcome (physical activity participation) occurred as a result of change in the psychological mediators, mediation analysis will be conducted using the Sobel test, which involves testing the null hypothesis that there is no difference between the total and direct effects, that is, the assumption that there are no indirect effects of the psychological mediators on physical activity behavior change [69]. This approach provides greater statistical power than the more traditional Baron and Kenney [70] approach. Given the small sample size present in the current study, this is an important consideration and should ensure Type II error is minimized.

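### The 90% power is for an unadjusted 5% test of the 3-month contrast, but the article tests that contrast with a Bonferroni correction that the sample size does not allow for

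*Protocol article*

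**What the plan says.** Three sections of the protocol article bear on this point.

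- **Aim.** The single hypothesis is that the intervention is "more effective than a leaflet for promoting participation in physical activity at three months follow-up". The 6-month question is the first of the secondary aims: "To test efficacy at six months follow-up (three months post-intervention".
- **Sample size.** The calculation is for one comparison of change between the groups: "31 participants per group are required in order to detect an effect of 63.83 minutes/week of moderate-vigorous physical activity participation". Its error rates and test are given as "This assumes power of 90%, 5% significance level with a two-sided unpaired" t-test, with the comparison made "between the intervention and control group using a pooled standard deviation of 75 minutes/week". After a 20% allowance for dropout, "up to 76 postnatal women will be sought". Multiplicity is not mentioned.
- **Data analysis.** The model is a repeated-measures ANCOVA with group as a between-subject factor and several covariates. Within it, Bonferroni post-hoc "testing will be used to investigate intervention efficacy (between-groups change to three months) and assess maintenance effects". The section does not say how many comparisons the correction covers, and it describes no separate, unadjusted test of the 3-month contrast.

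**The concern.** The 3-month contrast is the primary hypothesis in the Aim and the basis of the sample size, where it is one test at the full 5% level. In the Data analysis section the same contrast is one of two questions under a Bonferroni correction. On the natural reading, the primary question gives up part of its significance level to pay for a secondary one.

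Two things follow. The 90% figure describes a test other than the one the article sets out. It is also unclear which p-value, adjusted or not, decides the trial. This matters more in a trial of at most 76 women, whose analysis section itself points to the small sample and wants type II error kept low.

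**Working it through.** **Inputs (Sample size section).** Difference 63.83 min/week; SD of change 75 min/week; 31 per group; two-sided 5%; unpaired t-test; 20% dropout; up to 76 recruited. Equal allocation is implied by the equal group sizes.

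**Assumption.** The number of comparisons, m, is not stated. I show m = 1 (the correction does not touch the 3-month contrast), m = 2 (the two questions named in the text) and m = 3 (a wider family, such as all pairs of the three time points, which the text does not describe).

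**Formula.** Power = P(|T| > t_crit), where T is noncentral t with 2n − 2 degrees of freedom and noncentrality (difference/SD) × √(n/2), and t_crit is the two-sided critical value at level 0.05/m.

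**Step 1: reproduce the plan's figure.** Standardized difference = 63.83/75 = 0.851. With n = 31, noncentrality = 0.851 × √15.5 = 3.351 and df = 60. At 0.05, t_crit = 2.000 and power = 0.909. With n = 30, power is 0.8999, just short of 90%. So 31 per group is the correct answer for a single unadjusted 5% test.

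**Step 2: apply the correction.**

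| Comparisons corrected for | Level | t_crit (df 60) | Power, 31 per group | Power, 30 per group |
|---|---|---|---|---|
| m = 1 | 0.05 | 2.000 | 0.909 | 0.900 |
| m = 2 | 0.025 | 2.299 | 0.8505 | 0.837 |
| m = 3 | 0.0167 | 2.463 | 0.8095 | 0.794 |

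The 30-per-group column is included because 76 × 0.8 = 60.8, about 30 per group.

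With 31 per group, type II error is 1 − 0.909 = 0.091 at m = 1, 1 − 0.8505 = 0.1495 at m = 2 and 1 − 0.8095 = 0.1905 at m = 3.

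**Step 3: size needed to keep 90%.** For m = 2, 36 completers per group (power 0.904), or 72/0.8 = 90 randomized. For m = 3, 39 per group (power 0.902), or 78/0.8 = 97.5, so 98 randomized.

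**Step 4: what could offset the loss.** Covariates reduce the residual SD to 75 × √(1 − R²). Allowing 5 degrees of freedom for them (df = 55) and keeping 31 per group, R² = 0.14 gives power 0.901 at level 0.025, and R² = 0.22 gives 0.903 at level 0.0167. With no dropout at all (38 per group), unadjusted for covariates, power is 0.920 at m = 2 and 0.893 at m = 3.

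**The case against.** The strongest objection is that the article never states the family of comparisons. With only two groups, a correction applied separately within each time point covers one comparison and costs nothing. A reader might infer that the level applied is definitely 2.5% or 1.67%. The text does not support that: 2.5% is the natural reading because two questions are named together, and 1.67% has little basis in the wording.

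A reader might also infer that 90% power is certainly not achieved. That too goes beyond the documents. The figures above are for an unpaired t-test, whereas the planned model adjusts for covariates, and those explaining about 14% of the variance in change would restore 90% at level 0.025. The article gives no such figure and claims no such gain, and its example covariates do not name baseline activity, so the gain is possible but unproven. Better retention than planned would also help, but the plan itself allows for 20% dropout.

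Bonferroni is conservative: it does not inflate false positives or bias the estimate, and correcting across two time points is a legitimate choice. The Discussion itself calls the expected evidence tentative. These points lower the severity.

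It can also be said that a condensed article leaves the allocation of the significance level to an analysis plan. That explains why m is missing, but not the mismatch. The article does say how 3-month efficacy is tested, and what it says differs from the basis of its sample size.

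**Conclusion.** The point holds as a mismatch that should be fixed. The sample size treats the 3-month comparison as a single unadjusted 5% test; the analysis section places it under Bonferroni together with the 6-month question, with no allowance in the numbers.

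If the two named contrasts share the correction, power at 31 per group is about 85% instead of the stated 90%, and type II error rises from about 9% to about 15%. This rests on m = 2, the article's own difference and SD, and no gain from covariates. The range is 81% (m = 3) to 90.9% (no effect on the primary contrast). The validity of a positive result is not in question. The harm is a greater chance of missing a real effect on the primary question, and a power statement that belongs to a different test.

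**What to change.** Make one of two changes before outcome data are examined.

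1. **Preferred.** State that the between-group contrast in weekly moderate-vigorous activity at 3 months is the single primary test, two-sided 5%, without Bonferroni adjustment, and that 6 months is secondary. One way to handle 6 months is to test it second in a fixed sequence, claiming a confirmatory result only if the 3-month test is significant. That keeps the family-wise error over the two contrasts at 5% and agrees with the existing sample size.
2. **If Bonferroni is kept across both contrasts.** State that two comparisons are corrected for, and restate the power as about 85% at 31 per group.

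Either change takes a sentence or two and no extra data. The small downside of the fixed sequence is that no confirmatory 6-month claim is possible if 3 months is not significant. The second option instead accepts the lower power.

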## Discussion

Results from this study will be available by the end of 2012. The strengths of this study include the use of a randomized, controlled design, objective measures of physical activity change and a three-month post-intervention follow-up point (six months from baseline). Using this approach, the MAMMiS study will address many of the methodological shortcomings of previous trials. Results from this study may also provide valuable information to inform future physical activity promotion studies with postnatal women. In particular, this trial will provide tentative evidence on the efficacy of a motivational and behavioral intervention including group pram-walking in a UK-setting. As the intervention techniques used in this study have been defined according to previously published taxonomies [43,44] (for specific details on intervention techniques please contact [name]), the intervention will be easily reproducible. The intervention is potentially generalizable as two physical activity consultations and a 10-week group pram-walking program conducted locally, once per week is at a reasonably low intensity and the intervention could be delivered by a suitably trained person. However, as the present study tests the efficacy of the intervention at a single-site (assessments and interventions are carried out by a single investigator), further testing across multiple sites would be required to address intervention effectiveness in other contexts (for example, different populations, delivery by different researchers/practitioners).

Other strengths of this study include: conducting mediation analysis to help identify whether psychological constructs targeted through the intervention were in fact responsible for changes in physical activity behavior; including health and well-being measures enabling information to be gathered on the potential impact of physical activity change, which may aid in sample size calculations for future studies interested in these outcomes; and finally, the inclusion of a qualitative arm at the end of the trial will help assess intervention acceptability among postnatal women. These features, alongside outcome and process data, will help advance our understanding of physical activity behavior change in postnatal populations.

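### The mediation analysis is given a causal reading, but the mediator-to-activity path is not randomized and a Sobel test alone cannot support that reading

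*Protocol article*

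**What the plan says.** The Data analysis section opens its mediation paragraph with a causal question: "To assess whether change in the main outcome (physical activity participation) occurred as a result of change in the psychological mediators". The method is fixed in the same sentence: "mediation analysis will be conducted using the Sobel test", described as a test of whether the total and direct effects differ. The only reason given for this choice is better power than the older causal-steps approach.

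The Discussion counts the analysis among the study's strengths, as helping to identify "whether psychological constructs targeted through the intervention were in fact responsible for changes in physical activity behavior".

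Earlier in Data analysis, in the description of the repeated-measures ANCOVA, the article says: "Covariates, which have been shown to influence physical activity participation, will be included". Its examples are age, BMI and stage of change, followed by infant's age and number of children. The same approach is extended to the secondary outcomes. The mediation sentence neither names covariates nor says that there are none.

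The Randomization section assigns women to groups. Nothing assigns them to levels of self-efficacy, planning or any other mediator.

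**The concern.** The indirect effect is the product of two coefficients: allocation on mediator (a), and mediator on activity given allocation (b). Randomization protects a and the total effect. It does not protect b. If something unrelated to the construct improves both a woman's questionnaire score and her accelerometer minutes, b is non-zero even when the construct does nothing. Because a is real, the product then looks like mediation.

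The Background says that knowing whether interventions changed the proposed mediators is needed to improve future interventions. A construct credited wrongly would be carried forward as an active ingredient. Several mediators are to be tested, so there are several chances of this. The article states no assumption of no shared causes, no sensitivity analysis and no caution next to the causal wording.

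**Working it through.** **1. The plan's own figure.** The Sample size section states that "31 participants per group are required in order to detect an effect of 63.83 minutes/week", "using a pooled standard deviation of 75 minutes/week", at 90% power and 5% two-sided. The standardized effect is 63.83/75 = 0.85. The noncentral t distribution gives power 0.8999 with 30 per arm and 0.909 with 31. So 31 per group reproduces and is not in dispute. The article gives no figure for the mediation analysis.

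**2. Set-up for the check.**
- From the article: 31 per arm (62 analysed), SD of change 75 min/week, total effect 0.85 SD, Sobel test at 5% two-sided.
- Assumed, because the article gives neither: a = 0.8 to 1.2 SD; one shared cause with loading λ = 0.3, 0.4 or 0.5 on the change in both variables.
- True mediator-to-activity effect: zero.

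**3. Size of the false indirect effect.** With unit residual variances, the shared cause gives a residual mediator-activity correlation of λ². The regression of activity on mediator given allocation therefore returns b = λ² instead of 0. In minutes the false indirect effect is a × λ² × 75.
- λ = 0.3: 0.8 × 0.09 × 75 = 5.4, up to 1.2 × 0.09 × 75 = 8.1 min/week
- λ = 0.4: 0.8 × 0.16 × 75 = 9.6, up to 1.2 × 0.16 × 75 = 14.4 min/week
- λ = 0.5: 0.8 × 0.25 × 75 = 15.0, up to 1.2 × 0.25 × 75 = 22.5 min/week

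Against the design effect, the middle row is 9.6/63.83 = 15% to 14.4/63.83 = 23%.

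**4. How often the test declares mediation.** The statistic is z = ab / √(a²·SE_b² + b²·SE_a²), with rejection at |z| > 1.96. Simulation used 4,000 trials per setting; the ranges cover a = 0.8 to 1.2 SD and repeated runs.

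| Loading λ | Residual correlation λ² | Sobel test significant |
|---|---|---|
| 0 | 0 | about 1-3% |
| 0.3 | 0.09 | about 4-7% |
| 0.4 | 0.16 | about 10-19% |
| 0.5 | 0.25 | about 25-43% |

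A parallel simulation that sets the residual correlation directly, with a = 0.8 SD, gives 16%, 38% and 81% at correlations 0.2, 0.3 and 0.5. With a = 0.5 SD it gives 5%, 14% and 37%.

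**5. What covariates can do.** At λ = 0.4, adjusting for the whole shared cause, perfectly measured, brings rejection back to about 2-4%. Adjusting for a covariate that correlates only 0.3 (assumed) with it leaves about 8-16%. Listed covariates help only as far as they stand in for the shared cause.

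**6. How fragile a significant result would be.** SE_a = √(2/31) = 0.254, so a/SE_a is 0.8/0.254 = 3.15 to 1.2/0.254 = 4.72. Since 1/z² = 1/z_a² + 1/z_b², reaching z = 1.96 needs z_b = 2.50 (for 3.15) or 2.15 (for 4.72). With 62 − 3 = 59 degrees of freedom, the residual correlation is z_b/√(z_b² + 59), which is 0.31 or 0.27. A just-significant result would therefore be fully explained by a shared cause loading √0.31 = 0.56 or √0.27 = 0.52 on both changes.

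**The case against.** **The charge that covariates are left out.** A reader might infer that the plan excludes covariates from the mediation models, because they are named only for the ANCOVA. The article does not say so. It is silent, and a condensed article commonly leaves such detail to the full plan. That reading is not supported and forms no part of the point.

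**Named shared causes.** One might also infer that the Background identifies childcare and tiredness as common causes of confidence and activity. It speaks of confidence in the face of such barriers, which defines the self-efficacy construct. Shared causes are plausible, but the article does not state any.

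**Change scores.** It is tempting to call the use of change wrong and to require three-month values adjusted for baseline. That does not hold either. With an unmeasured stable cause loading 0.4 to 0.7 on both variables at both waves, a = 1.0 SD and no true mediator effect, change scores give about 0 min/week and 1-2% rejection. The baseline-adjusted model gives about 9-19 min/week and 9-40%. In the opposite case, baseline mediator and baseline activity correlated 0.2 to 0.5 with no shared cause of change, change scores carry 3-7 min/week of false effect, which baseline adjustment removes. The documents cannot settle which structure applies.

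**Strength of the claim.** The Discussion wording is softened to helping identify, and secondary aim 3 speaks of predicting change. Both are true. The causal question in Data analysis carries no such softening.

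**Generality.** Unmeasured confounding of mediator and outcome affects any trial mediation analysis, and at a loading of 0.3 the error rate is close to the nominal 5%. This limits the severity. It does not justify a causal reading without a stated assumption.

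**Conclusion.** The point holds as a mismatch between the stated conclusion and what the analysis can show. A significant Sobel test here is compatible with mediation and equally with a shared cause of the two changes. Under the assumed loadings of 0.3, 0.4 and 0.5, an inert mediator is declared significant in about 4-7%, 10-19% and 25-43% of trials, with false indirect effects of about 5-8, 10-14 and 15-23 min/week. These figures show how sensitive the test is; they do not predict what this trial will find, since the article gives neither the loadings nor the mediator effects. The issue is confined to the mediation question behind secondary aim 3 and leaves the comparison between randomized groups untouched. It should be corrected because the remedy is nearly free and changes what that aim may conclude.

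**What to change.** 1. State that both mediation regressions include the covariates already collected for the ANCOVA, and that these remove only part of the bias.
2. For each mediator, report the residual mediator-activity correlation that would bring the indirect effect to zero. In linear models without an allocation-by-mediator interaction, this is the partial correlation of mediator and activity given allocation and covariates.
3. In Data analysis and in the Discussion, replace the causal wording with: consistent with mediation, assuming no unmeasured shared causes.
4. Keep change scores as the analysis. At most, show baseline-adjusted three-month values beside them, noting that each is biased under a different confounding structure.

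Cost: the five example covariates use about 5 of the 59 residual degrees of freedom if each enters as one term. There is one extra analysis and a weaker stated conclusion. No new data are needed.

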#### Psychological mediators

Psychological mediators are measured *via* a self-completion questionnaire that has been developed for this study from adapted measures used in previous studies [58-62]. The reliability of all questionnaire items will be tested in the study using Cronbach’s alpha for each proposed mediator, which are measured using 4 to 7-point Likert scales (for example, very unlikely – very likely, completely untrue - completely true *etc.*). Mediators measured in this study are specifically those targeted by the intervention methods (*for example,* outcome expectancies, self-efficacy, intentions to be active, action and coping planning and self-regulatory actions). Self-efficacy (*for example,* “How confident are you that you can be regularly physically active during the next three months…even if I’m tired”, and so on*.*) and outcomes expectancy measures (“If I were regularly physically active during the next three months…I would be healthier” and so on*.*) were sensitive to the most frequent barriers and enablers to activity cited by postnatal women; taken from a survey 667 postnatal women [63]. Intentions are operationalized using one item: “During the next three months do you intend to be regularly physically active?” [58]. Action planning is measured using four items following the stem: “I have made a detailed plan about being regularly physically active during the next three months…” (for example, how/when/where/how often). Coping planning, in contrast, asks participants to rate three items; for example, the extent to which they “have a detailed plan about what to do if things get in the way of them being regularly physically active during the next three months”. Planning measures have been validated in previous studies [61]. Six items are used to measure self-regulatory effort, adapted from the action control questionnaire used by Sniehotta *et al.*[62]. Example statements are: “During the last three months…I have been aware of how much physical activity I should be doing to meet my personal standards. I have made sure to monitor how much physical activity I’ve done and I have tried really hard to be physically active.”

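### The Sobel test does not minimize type II error in this small sample: it beats causal steps only in some settings, and joint significance or a percentile bootstrap has more power

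*Protocol article*

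**What the plan says.** Under Data analysis the protocol article states that "mediation analysis will be conducted using the Sobel test". The reason is comparative: "This approach provides greater statistical power than the more traditional Baron and Kenney [70] approach". The next sentence draws the conclusion: "Given the small sample size present in the current study, this is an important consideration and should ensure Type II error is minimized". No other test of the indirect effect is mentioned, and neither mediation power nor path sizes are given.

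The number available comes from the primary outcome. Under Sample size, "31 participants per group are required in order to detect an effect of 63.83 minutes/week of moderate-vigorous physical activity participation", and "Assuming a 20% dropout (in line with similar studies [14,17]) up to 76 postnatal women will be sought". The constructs to be tested are listed under Psychological mediators: "outcome expectancies, self-efficacy, intentions to be active, action and coping planning and self-regulatory actions". Examining these mediators is the third secondary aim (Aim).

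**The concern.** The Sobel statistic refers the product of two estimated coefficients to a normal distribution. In small samples that product is skewed and heavy-tailed when the paths are modest, so the normal reference makes the test too cautious. The article cites the small sample as the reason for using Sobel, yet a small sample is where this caution costs most.

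What is at stake is how null results are read. If a targeted construct does carry part of the effect and the test misses it, a reader told that type II error had been minimized would give that null more weight than it deserves. The article presents the mediation analysis as a strength and as guidance for later interventions.

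**Working it through.** **1. Sample size.** Inputs from Sample size: difference 63.83 min/week, SD 75, two-sided 5%, power 90%. The standardized effect is 63.83/75 = 0.851. The exact two-sample t-test needs 30.007 per group, rounded up to 31, with power 0.909 at 31. The plan's figure reproduces. So 2 × 31 = 62 are evaluable as planned, and 76 is the most if nobody drops out. Both sizes are used below.

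**2. Why Sobel is conservative.** Let a be the group effect on the mediator, b the mediator effect on the outcome given group, and z_a, z_b their test statistics. Dividing ab by its first-order standard error gives

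z_Sobel = |z_a z_b| / √(z_a² + z_b²).

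This is always below the smaller of |z_a| and |z_b|. If both equal 1.96, z_Sobel = 1.96/√2 = 1.39, far from significance. With equal statistics, each must reach 1.96 × √2 = 2.77. Joint significance asks only that both exceed the critical value. With a common normal critical value, every Sobel rejection is therefore also a joint-significance rejection, whatever the paths. Joint significance still holds its level: when the indirect effect is null at least one path is zero, and that path is significant at most 5% of the time.

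**3. Size of the gap.** Simulation model: 1:1 randomization, M = aX + e, Y = bM + c′X + e, unit residual SDs, one mediator, two-sided 5%. The paths a, b and c′ are assumptions. The direct effect c′ does not alter Sobel, joint significance or the bootstrap; it matters only for causal steps. Rows with three figures use 2,000 replicates and 1,000 bootstrap draws, so the Monte Carlo standard error near 50% is √(0.25/2000) = 1.1 points.

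Power (%):

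| N | a | b | Sobel | Joint significance | Percentile bootstrap |
|---|---|---|---|---|---|
| 62 | 0.5 | 0.3 | 13.4 | 31.4 | 30.1 |
| 62 | 0.65 | 0.35 | 32.8 | 52.6 | 52.6 |
| 62 | 0.8 | 0.3 | 34.8 | 54.5 | 54.9 |
| 62 | 0.8 | 0.4 | 56.4 | 73.4 | 73.2 |
| 62 | 1.0 | 0.39 | 70.4 | 81.2 | 82.3 |
| 62 | 1.0 | 0.5 | 88.0 | 93.3 | – |
| 62 | 1.0 | 0.59 | 93.0 | 96.0 | 96.5 |
| 62 | 1.2 | 0.59 | 97.8 | 98.4 | 98.2 |
| 76 | 0.5 | 0.3 | 21.0 | 40.8 | 41 |
| 76 | 0.65 | 0.35 | 46.6 | 66.2 | 66 |
| 76 | 0.8 | 0.4 | 73.0 | 85.0 | 85 |

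(The row a = 1.0, b = 0.5 and the N = 76 rows come from separate runs. The N = 76 bootstrap figures are rounded.)

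For a = 0.5 to 0.8 and b = 0.3 to 0.4 the shortfall runs from 85.0 − 73.0 = 12 points to about 53 − 32 = 21 points in a repeat run at N = 62, a = 0.65, b = 0.35. At a = 1.0, b = 0.5 it is about 5 to 6 points across runs, and it is smaller beyond that.

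**4. False positives (%, nominal 5).**

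| N | Zero path | Sobel | Joint significance | Percentile bootstrap | Bias-corrected bootstrap |
|---|---|---|---|---|---|
| 62 | b (a = 0.85) | 1.6 | 4.2 | 4.9 | 7.5 |
| 62 | a (b = 0.39) | 1.0 | 3.5 | 3.5 | 6.7 |
| 76 | b (a = 0.85) | 2.2 | 5.0 | 5.9 | 8.8 |
| 76 | a (b = 0.39) | 1.7 | 4.9 | 5.0 | 8.2 |

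The Monte Carlo standard error at 5% is √(0.05 × 0.95/2000) = 0.5 points. The power gain does not come from a materially inflated error rate, except with the bias-corrected version.

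**5. The comparison the article does make.** Causal steps here is joint significance plus a significant total effect, so the result depends on the total effect ab + c′. At N = 62, Sobel against causal steps:

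- a = 0.8, b = 0.39, c′ = 0 (total 0.31): 55.4% against 16.8%.
- a = 0.8, b = 0.4, c′ = 0.2 (total 0.52): 58.2% against 37.3%.
- a = 0.8, b = 0.4, c′ = 0.53 (total 0.85): 56.8% against 65.0%.
- a = 0.5, b = 0.3, c′ = 0.70 (total 0.85): 13.3% against 28.5%.

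The last two set the total to the planned 0.85, read in residual-SD units.

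**The case against.** The strongest reply is that the disputed sentence depends on the one before it. Read together, the article says only that Sobel is preferable to causal steps in a small sample, and that is true when the direct effect is zero or modest (step 5). This part stands. A reader might infer that the article has the facts reversed, or that Sobel is the weakest choice. The documents do not support that: the only comparator named is causal steps, and Sobel beats it over part of the range. But the article goes on from a better test than one rival to the least possible type II error, and the hedged verb does not make that step valid.

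Second, the article gives no path sizes, so the size of the gap is assumed. This stands, and the gap becomes small when both paths are large. The ordering of Sobel and joint significance in step 2 does not depend on the paths.

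Third, at small paths every test is weak: at a = 0.5, b = 0.3 and N = 62 the bootstrap still misses about 70% of true effects. This stands. Changing the test reduces the loss but does not make the analysis well powered.

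Fourth, covariates, several mediators together and skewed activity minutes were not simulated. With several constructs tested, Sobel's caution also gives some incidental protection against false positives. This limits the precision of the figures, but unplanned conservatism is not a multiplicity rule, and the article offers Sobel for its power.

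Finally, modelling detail may sit in an analysis plan that is not shown. That is fair for covariates and resampling settings, but the article itself fixes the test and states the reason for it.

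**Conclusion.** The statement that type II error is minimized is wrong and should not stand. At 62 to 76 participants Sobel uses only about 1 to 2% of its nominal 5% when one path is zero. It gives up about 12 to 21 points of power for small-to-medium paths and about 6 points or less when both are large. These sizes rest on assumed paths, a single mediator, normal errors and no covariates.

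Two stronger readings should be resisted. The claim that Sobel beats causal steps is conditional on the total effect; it is not simply false. Nor is the mediation analysis invalid: Sobel errs towards missing effects, so a significant Sobel result is not made suspect by this point. The primary analysis and its sample size are untouched. The matter is confined to secondary aim 3, but it is worth correcting because the remedy is specific and nearly free.

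**What to change.** In Data analysis, name either a 95% percentile-bootstrap confidence interval (not bias-corrected) or the joint-significance test, at two-sided 5%, as the test of each indirect effect in place of Sobel. Delete the sentence claiming that type II error is minimized. If the comparison with causal steps is kept, say that it depends on the size of the direct effect. Covariates and the number of resamples can be left to the analysis plan.

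The cost is a few lines of code, one changed sentence and a slightly less conservative test, with bootstrap false positives up to about 6% in the settings examined. No further data are needed.
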